## Abstract

**Background:**

Despite their potential as low-threshold, low-cost and high-flexibility treatments of depression, behavioural activation and physical exercise have not yet been directly compared. This study will examine the effects of these interventions, administered via the Internet. The added effect of providing a treatment rationale will also be studied, as well as a relapse prevention program featuring cognitive behavioural therapy components.

**Methods/Design:**

This randomised controlled trial will include 500 participants meeting the diagnostic criteria for major depression, recruited in multiple cycles and randomised to either a waiting list control group with delayed treatment, or one of the four treatment groups: (1) physical exercise without a clear treatment rationale; (2) physical exercise with treatment rationale; (3) behavioural activation with treatment rationale; or (4) behavioural activation without a clear treatment rationale. Post treatment, half of the participants will be offered a relapse prevention program. Primary outcome measure will be the Patient Health Questionnaire 9-item. Secondary measures include diagnostic criteria for depression, as well as self-reported anxiety, physical activity and quality of life. Measurements - done via telephone and the Internet - will be collected pre-treatment, weekly during treatment period, immediately post treatment and then monthly during a 24-month follow-up period.

**Discussion:**

The results of this study will constitute an important contribution to the body of knowledge of the respective interventions. Limitations are discussed.

**Trial registration:**

ClinicalTrials.gov: NCT01619930

## Background

It is well recognised in clinical and research settings that patients with depression account for a large portion of those seeking healthcare. In a large study of the 12-month and lifetime prevalence of mental disorders among the European population, major depression was found to be the single most common disorder with a lifetime prevalence of 12.8% and a 12-month equivalence of 3.9% [1]. In the year 2020 it is expected that depression will be the world-wide second largest disease-related cause of disability, second only to heart disease [2]. In addition to the personal suffering involved, depression is a major source of economic strain for society. The total annual cost of depression in Europe in 2004 has been estimated to €118 billion, corresponding to 1% of the total European economy at the time [3].

Treatments of depression include both pharmaceutical (antidepressants) and psychological (psychotherapy), with research showing near-equal efficacy between them [4]. Unfortunately, research also indicates that far from all who suffer from depression seek treatment [5]. A wider treatment arsenal including low-cost, high-flexibility treatments is therefore desirable. One promising treatment is activation, two kinds of which are behavioural activation, and one solely focused on physical exercise. These two kinds of activation therapy have the potential to be administered via the Internet, which would both lower the threshold for those seeking treatment, while also providing effective treatment to a low cost. In this therapeutic context, physical exercise can be considered a focused form of behavioural activation [6] in the respect that both interventions require the client to schedule and perform activities. A recent innovative randomised controlled trial comparing aerobic exercise to low-intensity stretching - both treatment arms having equal levels of activity frequency and social interaction - found no between-group difference in antidepressant effect [7]. An explanation for this result could be that it was the common activation component that caused the antidepressant effect, rather than the physical exercise *per se*. At present it is unknown whether any antidepressant effects of behavioural activation and physical exercise are treatment-specific or due to the common activation factor. Using an advanced trial design, the study herein described will be able to evaluate the antidepressant effects of both the respective treatments in themselves, and compare the two.

Strategies now known as behavioural activation (BA), originally developed by Lewinsohn and colleges in the 1970s, focused on pleasant events scheduling and BA is now defined as a structured, brief psychotherapeutic method to: (1) increase engagements in adaptive (appetitive) activities; (2) decrease engagements in activities that maintain or increase depression; and (3) increase access to reward [8]. A 2007 meta-analysis found BA to have a large effect on depressive symptoms, with the added benefit of being relatively uncomplicated, time-efficient and not requiring complex skills of patient or therapist [9]. Explaining the BA treatment rationale to patients is widely considered an early step in treatment [6], yet the component-specific effect of providing this rational has not yet been the subject of research. Acknowledging the well-known effect on outcome in cognitive behavioural therapy of the client’s acceptance of treatment rationale [10], this study will be able to distinguish the effect of providing a clear and extensive treatment rationale in BA therapy. This study will also be the first to test whether BA therapy can be adequately administered via the Internet (see [6,11]).

A 2007 Cochrane review found physical exercise to have a large clinical effect on depression. If however the methodologically weak studies were excluded, the clinical effect was moderate and non-significant [12]. Acknowledging the methodological weaknesses of previous studies, a more recent meta-analysis including only randomised controlled trials suggests a large and significant effect of physical exercise on depression [13]. It should be noted that the causality of physical exercise as treatment of depression has been questioned. In a large population-based study, De Moor *et al*. [14] found that in genetically identical twins, the twin who exercised more did not display fewer symptoms of depression, suggesting that the causal role should be ascribed to a common genetic factor rather than the exercise itself. Indeed, the specific mechanism by which physical exercise has an effect on depression, if any, is still unknown. As is the case with BA therapy, no previous research has studied the unique, component-specific effect of providing a clear treatment rationale. Providing this rationale may increase the patient’s motivation to exercise, which in itself may give a direct placebo-type antidepressant effect and/or indirectly reduced depressive symptoms following increased physical activity (which can be measured). This trial will be the first to study the component-specific effect of providing a clear treatment rationale in physical exercise therapy for depression.

In addition to studying the effects of Internet-administered physical exercise and BA - with and without providing a clear treatment rationale - and comparing them, this trial will include a depression relapse prevention program featuring cognitive behavioural therapy (CBT) components. Within 15 years, depression relapses may occur in as much as 90% of those experiencing an acute depression episode [15]. Psychotherapeutic interventions have been shown to effectively reduce the risk of depression relapses [16], yet no previous study has examined whether this type of intervention can be administered via the Internet (see [11]). With there being ample evidence for the effects of Internet-based CBT on depression [17], a CBT-style relapse prevention program delivered via the Internet holds great potential. This trial will feature such a program, provided after the physical exercise or BA intervention.

## Methods/Design

### Design

This randomised controlled trial has been registered in clinicaltrials.gov (NCT01619930). It will feature four treatment groups and a waiting list control group with delayed treatment: (1) physical exercise without treatment rationale; (2) physical exercise with treatment rationale; (3) BA with treatment rationale; (4) BA without treatment rationale; and (5) a waiting list control group, the participants of which will be randomised evenly to the four treatment groups after a 12-week delay. Participants will be recruited in several cycles over an estimated period of 1 year, with the participants of every cycle being evenly distributed to the five groups. Even distribution of participants to the different cycles will be pursued. After the treatment period of 12 weeks, 50% of each of the four treatment groups will receive a relapse prevention program. All participants will be monitored for 24 months post treatment (Figure 1).

**Figure 1 F1:**
[figure not shown]
**Flow diagram of the trial. **PE, physical exercise; BA, behavioural activation; RP, relapse prevention program.

### Screening and participants

Participants will be recruited nation-wide by means of advertisements in press and on the Internet. Application is done online, where prospective participants will also find further information on the study as well as the questionnaires serving as screening instruments. Before final inclusion, participants are required to provide written, informed consent.

The study population will consist of adults with diagnosed major depression according to DSM-IV-TR [18] criteria, with depression being the primary diagnosis. A score of 15 to 35 on the self-rated version of the Montgomery-Åsberg Depression Rating Scale (MADRS-S) [19] is also required. Other inclusion criteria include: living in Sweden and being able to read Swedish; being at least 18 years old; and having access to a computer with an Internet connection. Use of psychoactive medication is not grounds for non-inclusion if the dosage has been stable for the past 3 months and will continue to be stable during the intervention period. Any changes in medication during the study period will be noted along with the other measurements at treatment completion and at the 12- and 24-month follow-ups. If the proportion of patients who use pharmacotherapy differs between the treatment groups we will use pharmacotherapy metrics as factors in the mixed model analysis to adjust for a possible confounder effect when treatment effects are studied. Individuals meeting diagnostic criteria for treatment-demanding additional psychiatric conditions (for example, schizophrenia and bipolarity) will be excluded and referred to healthcare services. Individuals deemed suicidal or too severely depressed will also be excluded, the latter indicated by the scoring of item 9 on MADRS-S concerning the risk of suicide. When in doubt, a telephone interview will be conducted. Individuals currently receiving other psychological treatment will be excluded.

Initial selection of participants will be based on the results of the online screening instruments, consisting of MADRS-S, PHQ-9 [20], IPAQ [21], QOLI [22], GAD-7 [23] (see below) and a number of additional questions on demographics and previous treatment experiences. While the other instruments return as outcome measures (see below), MADRS-S will only be used in the screening procedure as a measure of the severity of depression symptoms. Previous research has shown that MADRS-S has a good internal consistency (Cronbach’s alpha 0.85 to 0.94), a satisfactory singe-component factor structure (47% to 69% variability explanation power), and a good correlation (Pearson’s correlation 0.81 to 0.91) with the clinician-rated version [24]. The psychometric properties of the Internet-administered version of MADRS-S has found to be sufficiently similar to the pen and paper version [25,26].

Prospective participants meeting initial inclusion criteria will be interviewed via telephone according to the Mini-International Neuropsychiatric Interview (MINI) [27] manual. Diagnostic interviews conducted per telephone have previously been found to be in very good agreement with face-to-face interviews regarding major depressive disorder [28]. The screening interviews will be conducted by supervised, clinical psychology master’s students, trained in the use of MINI. The interviewers will meet together with experienced clinical psychologists and psychiatrists to discuss final inclusion and to tailor the respective treatment program to each participant. Randomisation of participants to the different groups will be done by a statistician not otherwise involved in the study, using a computer-generated list with variables not known to the principle researchers. Participants who drop out will not be replaced.

Participants will access treatment programs, register data and communicate with their therapists using an SSL-encrypted online interface. Participants will log in using their anonymous participant number, a chosen password and unique, single-use codes sent by SMS or ordinary mail.

The study aims to detect a moderate difference in the primary outcome measure (see section 2.4.3 below) with 80% power and a 5% significance level (Bonferroni-adjusted). In accordance with this, the study will feature 500 participants, with 100 in each treatment group (125 after the control group is dissolved and divided) and a total of 250 (half of each of the four treatment groups) receiving relapse prevention.

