### Analysis

The study design will allow for multiple comparisons: the two physical exercise groups (separately and together) will be compared to controls, as will the two BA groups (separately and together). In all other analyses, the groups in question will include those from the control group later randomised to interventions, this to increase the statistical power. The two physical exercise groups will be contrasted with the two BA groups. Further, the physical exercise group with treatment rationale (group 1) will be contrasted with the group without (group 2), and the BA group with treatment rationale (group 3) will be contrasted with the BA group without (group 4). Finally, the four groups receiving relapse prevention will be contrasted with the four groups that do not. At the 12- and 24-month follow-ups, within-group comparisons will be made with previous results.

A number of statistical analyses will be deployed. Treatment outcomes will be examined using mixed effect models, Bonferroni-correcting for multiple comparisons. This method is deemed preferable to uni- and multivariate repeated measures of variance [40], especially since the study has built-in data-loss. The Kaplan-Meier estimator will be used to estimate survival rates during the study period. To find potential predictors of treatment outcomes (including treatment adherence and drop-out), logistic regression analysis on background variables will be performed (see [41]).

Since all questionnaire data will be supplied directly by the participants through the online interface, there is no risk of data loss or data distortion along the way. Data will be stored encrypted and in unidentifiable form (using participant-numbers). Standard missing data analysis will determine if unexpected missing data due to participant drop-out are random or not.

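### Adjustment for pharmacotherapy hangs on an undefined observed group difference and is not restricted to use at screening

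*Protocol article*

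**What the plan says.** The rule is in the protocol article, Methods/Design, Screening and participants. Four statements bear on it.

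- Medication at entry is allowed "if the dosage has been stable for the past 3 months and will continue to be stable during the intervention period".
- Later changes are recorded: "Any changes in medication during the study period will be noted along with the other measurements at treatment completion". The same is done one and two years into follow-up.
- The next sentence is the rule: "If the proportion of patients who use pharmacotherapy differs between the treatment groups we will use pharmacotherapy metrics as factors". The remainder of that sentence places these factors in the mixed models and gives possible confounding as the reason.
- The Analysis section names the model: "Treatment outcomes will be examined using mixed effect models, Bonferroni-correcting for multiple comparisons". It does not mention the medication covariate.

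The article does not say when use is measured for the purpose of the rule, how a difference is judged, or which metrics would enter. The primary outcome is PHQ-9, collected weekly during treatment and monthly for 24 months afterwards.

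**The concern.** There are two separate problems.

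The first holds on any reading. Whether the covariate enters depends on what is seen in the data. If use is measured at screening, any difference between randomised groups is chance, and calling it a possible confounder carries an observational idea into a randomised comparison. Two treatment-effect models are then available, and an undefined criterion chooses between them.

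The second is conditional. The rule refers to use and to metrics without tying either to screening, and it directly follows a sentence about changes recorded after randomisation. Use after allocation can be a consequence of treatment or of how the participant is faring. Conditioning on it can then remove part of the effect or open a non-causal path. The stability condition covers only the intervention period, so nothing in the text holds medication constant during the 24-month follow-up. The relapse-prevention contrast falls in that period, and a relapse could itself prompt medication. The risk is therefore greatest there.

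**Working it through.** **Inputs.** From the article: 500 participants, 100 per group, mixed models, adjustment conditional on an observed difference. The article gives no figure for medication use, PHQ-9 standard deviation, drug effect or dependence of medication on symptoms. All of those below are assumptions. There is no stated figure on this point to reproduce.

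**Step 1: how often chance alone triggers adjustment.** Draw the number of users in each of five groups of 100 from the same binomial distribution and apply two possible meanings of a difference (3,000 simulated trials per row).

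| Assumed use | Chi-square p<0.05 | Largest gap at least 10 points |
|---|---|---|
| 20% | 4.6% | 44% |
| 30% | 4.7% | 57% |
| 40% | 4.8% | 65% |
| 50% | 5.1% | 68% |

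If only the four active groups count, the gap rule can be computed exactly. With F the binomial(100, p) distribution function and k = 4, P(gap at least 10) = 1 − Σₘ{[F(m+9) − F(m−1)]^k − [F(m+9) − F(m)]^k}, which is 33% at 20% use and 54% at 50% use. Either way, the undefined criterion largely decides which model is fitted.

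**Step 2: effect on the estimate if later use is entered.** Two arms of 100, 1,500 simulated trials per row, assumed treatment effect −0.50 on a scale with SD about 1. Medication use after randomisation follows logit P = log(0.3/0.7) + slope × current symptoms. Least squares is fitted with and without that use. Change = 1 − adjusted/unadjusted.

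| Slope | Drug effect | Use, control v treated | Unadjusted | Adjusted for later use | Change |
|---|---|---|---|---|---|
| 0 | 0 | 30% v 30% | −0.505 | −0.504 | nil |
| 0.5 | −0.6 | 31% v 26% | −0.468 | −0.475 | slightly larger effect |
| 1 | 0 | 33% v 24% | −0.506 | −0.432 | 15% smaller |
| 1 | −0.6 | 33% v 24% | −0.448 | −0.429 | 4% smaller |
| 2 | 0 | 37% v 24% | −0.501 | −0.335 | 33% smaller |
| 2 | −0.6 | 37% v 24% | −0.420 | −0.337 | 20% smaller |

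A second set-up on the PHQ-9 scale has 200,000 per arm, a true effect of 2.5 points, SD 5, and logit P = b₀ + s × y/5. With (b₀, s) = (−2, 1) the estimate goes from 2.50 to 2.28, and 1 − 2.28/2.50 = 9%. With (−1.5, 1.5) it goes from 2.51 to 1.99, and 1 − 1.99/2.51 = 21%. With a drug effect of −1.5 points the losses are 6% and 16%.

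**Step 3: allow for the rule being conditional.** With a p<0.05 trigger, adjustment is used in about 5% of trials at slope 0, 12-13% at 0.5, 26-28% at 1 and 51-54% at 2. Averaged over trials with no drug effect, the estimate is −0.467 at slope 1 (1 − 0.467/0.506 = 8% smaller) and −0.380 at slope 2 (1 − 0.380/0.501 = 24% smaller).

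**Step 4: allow for repeated measures.** The two PHQ-9 scenarios were refitted as a pre/post random-intercept model with group-by-time as the effect (an assumed form). Medication as a person-level factor leaves the effect unchanged (−2.47 v −2.47). As a time-varying factor it shrinks the effect by 7% and 16% with no baseline users, and by 1% and 4% with an assumed 30% of stable baseline users.

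**Step 5: the alternative.** Always including medication use at screening left the estimate equal to the unadjusted one in every Step 2 setting (for example −0.506 v −0.506). In that simulation screening use was unrelated to outcome, so the result shows absence of bias, not a gain in precision.

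**The case against.** A reader might infer that the plan commits to adjusting for medication changes after randomisation, and so adjusts away part of the treatment effect. The text does not say this. The trigger is the proportion who use medication, not the proportion who change it. The term echoes the eligibility sentence just before, and the whole paragraph concerns screening. A baseline-only reading fits equally well and removes no treatment effect.

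A reader might also place the main harm in the waiting-list comparison. Here too the text gives limited support. The rule refers to treatment groups, which the article mostly uses for the four active arms as distinct from the waiting list. The requirement of stable dosage limits on-treatment changes during those 12 weeks, although it does not rule out new starts. After week 12 there is no waiting list. Between active arms of similar efficacy, the mechanism in Step 2 would produce little or no bias.

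The largest attenuations come from cross-sectional least squares with adjustment always applied, which is neither the planned model nor the stated rule. Steps 3 and 4 show how far the figures fall when those features are allowed for. Adjusting for screening use after a chance imbalance also leaves the comparison essentially unbiased.

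All of this stands. Finally, an analysis plan that is not shown may define the metrics and the threshold. That would settle the details, but the article itself states a conditional rule, and making the model depend on observed imbalance is a poor choice however the threshold is set.

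**Conclusion.** The point holds in limited form. Certain from the text: adjustment depends on an observed difference with no test, threshold or time point, and the covariate is not restricted to screening. The treatment-effect model can therefore be chosen after seeing the data.

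Conditional: bias arises only if medication use after randomisation enters the model and that use responds to symptoms or treatment. It is then usually towards zero. Its size rests wholly on assumptions: nil when use is unrelated to symptoms, roughly 10-30% in the simple simulations with moderate to strong dependence and no drug effect, a few per cent or less with stable baseline users in a repeated-measures model, and slightly the other way in one weak-dependence setting. None of these figures is an estimate for this trial.

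The rule should be fixed, but the documents do not show that the primary result will be distorted, so this is not a point on which the trial stands or falls.

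**What to change.** Replace the conditional sentence with:

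> Psychoactive medication use at screening (yes/no) is a fixed covariate in every treatment-effect mixed model, regardless of balance. Medication started or changed after randomisation is not a covariate in the main model; it is described by arm and examined only in a labelled sensitivity analysis.

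Screening use precedes every allocation in the trial, including the later allocation of waiting-list participants to the four active groups, so the same covariate serves all contrasts. The cost is one degree of freedom and a change of wording. No new data are needed, because the eligibility criterion on stable dosage already requires medication use to be known at screening. Sample size and clinical procedures do not change.

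### The 80% Bonferroni-adjusted power has no visible drop-out allowance and, for one arm against control, depends on a small comparison family or an unclaimed precision gain

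*Protocol article*

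**What the plan says.** All references are to the protocol article.

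- **Screening and participants, target.** "The study aims to detect a moderate difference in the primary outcome measure", "with 80% power and a 5% significance level (Bonferroni-adjusted"). *Moderate* is given no number, and no Bonferroni divisor is stated.
- **Screening and participants, size.** From this target the article concludes that "the study will feature 500 participants", "with 100 in each treatment group (125 after the control group is dissolved and divided"), and that 250 will receive relapse prevention.
- **Screening and participants, drop-out.** "Participants who drop out will not be replaced". No drop-out rate or inflation of the sample appears.
- **Analysis, contrasts.** "the two physical exercise groups (separately and together) will be compared to controls, as will the two BA groups (separately and together"). Four more follow: exercise v BA, rationale v none within exercise, rationale v none within BA, and relapse prevention v none. Contrasts that do not involve the controls use the arms enlarged by the former waiting-list participants.
- **Analysis, method.** "Treatment outcomes will be examined using mixed effect models, Bonferroni-correcting for multiple comparisons". The family over which the correction runs is not named.

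**The concern.** The Analysis section contains ten between-group contrasts: three of exercise v control, three of BA v control, and four others. An unqualified Bonferroni correction is naturally read as covering all ten, which puts each at 0.05/10 = 0.005. At that level 100 per group looks slightly too small for a moderate effect. In addition, 100, 125 and 250 are used unreduced, although drop-outs are not replaced and the Analysis section itself expects some drop-out. The 125 also needs every waiting-list participant to stay through the 12-week delay and start treatment.

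The contrasts most exposed are those of one arm against control. They include the comparisons that give the first test of Internet-delivered BA. If one arm shows no significant effect, readers will weigh that result against a stated 80% power that the contrast may not have.

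**Working it through.** **Inputs from the document:** power 80%; overall alpha 5%, Bonferroni-adjusted; 100 per group, 125 per active arm after the controls are re-randomised; ten between-group contrasts.

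**Assumptions:** *moderate* = 0.5 SD (d); two-sided tests; k contrasts sharing the 5%; loss of 10% to 30%.

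**Formula.** Two-sample t test with n per group, alpha = 0.05/k, df = 2n − 2 and noncentrality d·√(n/2). Power is the probability that the noncentral t exceeds the critical value in either direction.

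**Step 1: can the plan's figure be reproduced?** Only for certain k, since neither d nor k is given. At n = 100 the noncentrality is 0.5 × √50 = 3.536.

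- k = 6 (the control contrasts alone): critical t = 2.665, power 80.7%; 99 per arm needed for 80%.
- k = 7: power 79.2% by the t test, 80.1% by the normal approximation.
- k = 10: critical t = 2.839, power 75.6%; 109 per arm needed. The normal approximation gives 76.7% and 107.

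So 100 per group matches 80% for a family of about six or seven with nobody lost.

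**Step 2: single arm v control with loss (complete cases, d = 0.5).**

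| k | no loss (100) | 10% (90) | 20% (80) | 30% (70) |
|---|---|---|---|---|
| 4 | 84.4% | 79.6% | 73.7% | 66.5% |
| 6 | 80.7% | 75.3% | 68.8% | 61.1% |
| 10 | 75.6% | 69.5% | 62.4% | 54.3% |

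In this simple calculation every family size from 4 to 10 is below 80% at 10% loss.

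**Step 3: the other contrasts at k = 10, d = 0.5.**

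| contrast | no loss | 20% loss |
|---|---|---|
| two pooled arms v control (200 v 100) | 89.4% | 79.2% |
| rationale v none (125 v 125) | 86.7% | 75.6% |
| exercise v BA, or relapse prevention v none (250 v 250) | 99.7% | 98.5% |

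With no loss, only the four single-arm contrasts fall short.

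**Step 4: sensitivity to *moderate* (k = 10, 100 v 100, no loss).** d = 0.40: 49.7%; 0.45: 63.4%; 0.50: 75.6%; 0.55: 85.2%; 0.60: 91.8%. Power reaches 80% at about d = 0.52.

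**Step 5: gain from baseline adjustment (k = 10).** With correlation r between pre-treatment and outcome PHQ-9, the residual SD is √(1 − r²), so the effective d is 0.5/√(1 − r²).

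- r = 0.3: d = 0.524; power 80.6% with no loss, 68.0% at 20% loss.
- r = 0.5: d = 0.577; power 89.2% with no loss, 78.8% at 20% loss.

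The document gives no value for r.

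**Step 6: Holm v Bonferroni.** Simulation of ten contrasts with a shared control, all four arms at d = 0.5 v control, the remaining contrasts null and the variance known. Mean power of a single-arm contrast rises from 77% to 82% with no loss and from 64% to 69% at 20% loss. Because the variance is taken as known, these figures compare with the normal-approximation 76.7%, not with 75.6%.

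**The case against.** A reader might infer that the stated 80% is simply wrong. The document does not support that, for four reasons.

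- **The family of ten is a reading.** The text never says that all ten contrasts share one 5%. The six control contrasts are the only ones that use 100-person arms, and a family of six reproduces 100 per group. This stands. It leaves room to lose only one participant per arm, however, since 99 are needed.
- **The effect size and drop-out rates are supplied here.** With no loss, the gap at k = 10 is about 4 points, or a detectable effect of about 0.52 instead of 0.50 SD. That difference cannot be told apart within an unquantified *moderate*. The 54% to 70% range rests entirely on assumed loss. This also stands.
- **The planned analysis is a mixed model on weekly PHQ-9, not a t test on completers.** It can use partial data from those who leave, so treating 20% loss as 80 v 80 is pessimistic, and a baseline correlation near 0.3 closes the no-loss gap. This stands too, but the sample-size statement claims no such gain, and r = 0.3 does not restore 80% at 20% loss.
- **An article may leave the effect size, divisor and attrition to a fuller document.** Agreed; their absence alone is not the point. The point is that the group sizes in print are unreduced beside a rule of no replacement, and that the multiplicity method in print can be improved at little cost.

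Bonferroni is valid, so moving to Holm corrects no error. It recovers power that the plan gives away.

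**Conclusion.** The 80% is not shown to be false. For the four single-arm v control contrasts it holds at d = 0.5 only under a family of about six with essentially no loss, or with a precision gain that the sample-size statement does not claim. If all ten contrasts share the 5%, an unadjusted test has 75.6% power with no loss and 69.5% to 54.3% at 10% to 30% loss. The pooled and rationale contrasts exceed 80% with no loss and slip just below it at 20% loss. The 250 v 250 contrasts are secure throughout. These figures rest on d = 0.5, two-sided testing, the chosen k and assumed loss rates. This should be fixed but is not a fatal defect.

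**What to change.** None of these changes needs extra participants.

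1. **Use Holm instead of Bonferroni** over a named list of week-12 PHQ-9 contrasts. It keeps the familywise 5% and never has less power. Relapse prevention begins only after week 12, so say whether that contrast belongs to the same family. Cost: no simple simultaneous confidence intervals. The gain shrinks when fewer contrasts carry a true effect.
2. **Adjust each contrast for pre-treatment PHQ-9**, which is already collected at screening. For waiting-list participants who later enter an active arm, name which pre-treatment value is used. Cost: protocol or SAP wording.
3. **Restate power per contrast** for the family actually used, giving the effect in SD or PHQ-9 points, the expected attrition (including during the waiting period) and any baseline correlation relied on. Cost: possibly a less favourable figure for the single-arm v control contrasts, which should be accepted and reported.

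Holm or baseline adjustment alone may not restore 80% under heavy loss: at 20% loss Holm gave 69%, and adjustment with r = 0.5 gave 78.8%. The restated power should therefore be calculated, not presumed to be 80%.
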